## Abstract

**ABSTRACT:**

**Introduction:**

Maternal undernutrition and infections during pregnancy may influence birth and long-term child development outcomes. Characterising the micronutrient, metabolomic and microbiome profiles of pregnant women and infants may elucidate the underlying biology of adverse birth outcomes and early child development in the first 1000 days.

**Methods and analysis:**

The Enhancing Nutrition and Antenatal Infection Treatment (ENAT) study was a 2×2 factorial, randomised clinical effectiveness study conducted in Amhara, Ethiopia from August 2020 to June 2022. We cluster-randomised pregnant women (n=2399) to receive either a nutrition intervention (iron-folic acid (IFA), iodised salt and balanced energy-protein supplementation for women with mid-upper arm circumference <23 cm) or routine care (IFA only), and individually randomised women to an infection control intervention (genitourinary tract infection screening-treatment and screening-treatment of stool parasites) or routine care (syndromic approach). Participants were followed until 1 month postpartum. A subset of 532 women-infant dyads were consecutively enrolled in the biospecimen substudy from July 2021 to August 2022. Specimens were collected at enrolment (<24 weeks) and antenatal care follow-up (third trimester), and 1–6 months postdelivery. A subset of ENAT mother–infant dyads (n=462) was enrolled in the Longitudinal Infant Development and Growth study that followed infants until 24 months postpartum, from February 2023 to June 2024. We will determine the impact of ENAT interventions on micronutrient status, inflammation biomarkers and metabolomic and microbiome profiles. We will also determine the association of these profiles with birth outcomes and infant neurodevelopment.

**Ethics and dissemination:**

These studies were approved by the Institutional Review Boards of Addis Continental Institute of Public Health (ACIPH/IRB/002/2022) and Mass General Brigham (2023P000461). Results will be disseminated to international stakeholders via peer-reviewed journals and locally via strategic dissemination sessions.

**Trial registration numbers:**

ISRCTN15116516 and NCT06296238.

STRENGTHS AND LIMITATIONS OF THIS STUDYData and biospecimens are from an understudied, high disease burden, rural region in Ethiopia, providing unique and novel insights into biologic mechanisms of adverse pregnancy outcomes and child development in similar settings.A variety of different biospecimens will provide a comprehensive profile of biological changes in women during and after pregnancy and infants in their early days.High-quality gestational age dating and birth weight measurement in the cohort.At the health centres where specimens were collected, we were not able to immediately flash freeze samples. For some samples (like stool), we used solution media to stabilise DNA/RNA and expression profiles at ambient temperature, until the samples could be frozen at the −80°C freezer at the local laboratory.There may be some sample-to-sample variability due to differences in day or time of sample collection, which we tried to standardise when possible (eg, first breastmilk expression of the day). Additionally, for urine iodine, we will be calculating a coefficient of variation of a 10% subset of the samples being tested.

## Introduction

 Inadequate prenatal nutrition and infection control contribute to adverse health and development outcomes in the first 1000 days of infants’ lives.^1 2^ In 2020, approximately 19.8 million babies were born with low birth weight (LBW) globally, with 27% in sub-Saharan Africa.^3^ Undernutrition in pregnancy may result in babies being born preterm (<37 weeks gestational age), with LBW (<2500 g) and/or small for gestational age (<10th percentile of the newborn size standards of the International Fetal and Newborn Growth Consortium for the 21st Century (INTERGROWTH-21st^4^)), all factors that may contribute to increased lifetime morbidity and potential neurodevelopmental delays in later years.^5^,^7^ One intervention to address these adverse outcomes is balanced energy-protein (BEP) supplementation during pregnancy for women, recommended by the World Health Organization (WHO) in regions of high population-level undernutrition. However, these recommendations were initially based on limited evidence, and the WHO recommended additional research to bridge this knowledge gap.^8^,^10^ In addition to optimised prenatal nutrition, there are potential benefits of treating genitourinary tract and helminthic infections to mitigate both adverse maternal and pregnancy outcomes related to inflammation during pregnancy.^2 8^

Ethiopia has a high population prevalence of undernutrition and infectious diseases among women of reproductive age. There are limited data on the impact of interventions to improve both prenatal nutrition and infection control on birth outcomes. To address this, our team conducted the Enhancing Nutrition and Antenatal Infection Treatment (ENAT) study in Amhara, Ethiopia. The ENAT study was a 2×2 factorial randomised clinical effectiveness study, where pregnant women were cluster-randomised to receive either nutrition intervention (including BEP) or routine care, and individually randomised to receive an infection control intervention package or routine care.^11^ The primary aims of the ENAT study were to measure the impact of maternal nutrition and infection control intervention packages on infant birth outcomes (infant weight and length). Secondary outcomes included LBW, preterm live birth, stillbirth, size-for-gestational age, newborn head circumference, maternal anaemia and maternal stress, among others. Primary results of the parent trial are forthcoming. We also conducted the Longitudinal Infant Development and Growth (LIDG) study, a longitudinal 24-month follow-up of a subset of ENAT dyads (n=462) to assess the impact of prenatal interventions on long-term child neurodevelopment among ENAT infants. The protocols of the ENAT and LIDG studies were previously published.^11 12^

In this manuscript, we detail the protocols of the ENAT–LIDG biospecimen substudy. There is limited evidence on the impact of prenatal nutrition interventions on maternal–infant biology during pregnancy, delivery and postnatally in low- and middle-income countries (LMICs). As part of a consortium of pregnancy BEP studies funded by the Gates Foundation, we will explore the impact of nutrition interventions, including BEP on multiomics profiles in pregnant women and their infants in LMICs.^13^,^15^ This substudy aimed to explore the impact of the ENAT interventions on maternal and infant metabolomic profiles, microbiome compositions, iodine and iron status, inflammation biomarkers and gut pathogens. It is crucial to understand the biological processes underlying fetal growth, preterm birth and child growth and development to develop effective interventions to mitigate maternal undernutrition and improve infant outcomes in these populations and settings.^16^,^18^ Using a variety of biospecimens (whole blood, blood serum, stool, urine and breastmilk) that were collected, we will investigate the biological mechanisms influencing molecular level changes as an effect of the prenatal ENAT interventions on birth outcomes and child growth and development until 24 months.

## Methods

### Study setting and population

The ENAT study was conducted in 12 health centres in Amhara, Ethiopia. For ENAT, pregnant women at ≤24 weeks gestation presenting for antenatal care at the study sites were enrolled in the study if they met the eligibility criteria. Women were excluded if they had a non-viable pregnancy at ≤24 weeks gestation, determined by a lack of heartbeat on the enrolment ultrasound or were unable to return for follow-up visits (typically >2 hours travel distance from health centre). Within the ENAT study, the biospecimen substudy was conducted in a subset of six health centres (three enhanced nutrition and three routine care centres) that had functional laboratory rooms and were accessible from the regional city/central laboratory (Ambesamie, Arbgebeya, Lalibela, Legdiya, Yifag and Yismala). The LIDG study enrolled the infants born to women included in these ENAT biospecimen health centres who intended to stay in the study catchment area after giving birth. Children with major congenital anomalies, severe morbidity or developmental disorders, acute symptoms of illness (eg, headache, vomiting or dizziness) or neonatal encephalopathy were excluded from the study.

### Study design

The ENAT study was a pragmatic, open-label 2×2 factorial, randomised clinical effectiveness study with cluster-randomisation of an enhanced nutrition package (ENP) intervention and individual-level randomisation of an enhanced infection management package (EIMP) intervention (figure 1). The detailed study protocol has been previously published^11^ and this protocol paper details the protocols for biospecimen collection and planned analysis.

**Figure 1 F1:**
[figure not shown]
Enhancing Nutrition and Antenatal Infection Treatment (ENAT) study and Longitudinal Infant Development and Growth (LIDG) child follow-up study design participant flow. Figure from *Impact of maternal antenatal nutrition and infection treatment interventions on Longitudinal Infant Development and Growth in rural Ethiopia: protocol of the LIDG child follow-up study* by Workneh *et al* 2024. EIMP, enhanced infection management package; ENAT, Enhancing Nutrition and Antenatal Infection Treatment; ENP, enhanced nutrition package; LIDG, Longitudinal Infant Development and Growth; RCT, randomised controlled trial.

The LIDG study was a follow-up cohort study to ENAT in which biospecimens and neurodevelopmental assessments of infants born to women in ENAT were collected/conducted to assess neurodevelopment over the first 24 months of life. Study visits for children were at approximately 12 months (enrolment), 18 months and 24 months, and included the following assessments: Hammersmith Infant Neurological Examination, eye-tracking, MRI, Bayley-III, electroencephalogram (EEG), anthropometrics, diet questionnaires, home environment, and child health assessments and biospecimens.^12^

### Study interventions

#### Enhanced Nutrition Package (ENP) Intervention

The ENP intervention consisted of (1) nutritional counselling, (2) monthly supply of high quality adequately iodised salt, (3) iron-folate (IFA) tablets and (4) women with an upper-middle arm circumference (MUAC) of <23 cm received a fortified balanced energy-protein (BEP) supplement monthly. The BEP supplement was a locally produced, micronutrient fortified, corn soya blend (World Food Programme Super Cereal). The nutrition routine care arm consisted of IFA provision.

##### Study nutrition supplements

###### Iron-folate (IFA)

Following Ethiopian Ministry of Health recommendations, the health system distributes 60 mg iron plus 400 ug folic acid supplements to be taken once daily during pregnancy to all women. Due to our formative work indicating hesitancy to take such supplements in fear of delivering ‘big babies’ and gastric irritation as a side effect,^19^ intensive counselling was provided to pregnant women in the ENP arm to encourage compliance, as well as compliance monitoring and resupply at ANC visits as needed.

###### Iodised salt

A regular monthly household supply of adequately iodised salt (Waff Manufacturing, 30–40 ppm potassium iodate, 600 g bottle) was provided to women in the ENP arm for household consumption, and they were encouraged to use approximately three pinches daily.

###### Fortified Balanced-Energy Protein (BEP)

A regular monthly supply of locally produced, micronutrient fortified, corn soya flour blend (Super Cereal, Faffa Food Share Company, Addis Ababa, Ethiopia) was provided to women in the ENP arm with a MUAC<23 cm at enrolment or any ANC visit. The composition of the BEP used is described in table 1.

**Table 1 T1:** Super cereal corn soya blend composition (per daily 200 g serving)

Nutrient	Units	ENAT CSB content(200 gm)	Recommended target*
Energy	Kcal	760	250–500 Kcal per daily serving†
Protein	gm	28	14–18 g†
Fat	%	12	10%–60% of energy
Vitamin A	mcg RE	2076	550–770‡
Vitamin D	mcg	22.1	10–15
Vitamin E	mg	16.6	16–19
Vitamin K	mcg	60	72–90
Vitamin B_1_	mg	0.4	1.2–1.4
Vitamin B_2_	mg	2.8	1.3–1.6
Vitamin B_3_	mg	16	14–18
Folic acid	mcg	220	400–600
Vitamin B_6_	mg	2.0	1.7–2.0
Vitamin C	mg	180	100–120
Calcium	mg	724	500–1500
Iron	mg	8	22–27
Iodine	mcg	80	209–290
Phosphorous	mg	560	300–700
Zinc	mg	10	15–20

* Targets are results of an Expert Consultation held at Bill and Melinda Gates Foundation.

† Energy balance from macronutrient: portion size can be doubled in settings of high energy gaps, such as maternal malnutrition and where prevalence of birthweightbirth weight is high.

‡ Macronutrient recommendations were primarily based uponon Institute of Medicine () estimated average requirements () and recommended dietary allowances () values.

CSB, corn soya blend; ENAT, Enhancing Nutrition and Antenatal Infection Treatment.

### Enhanced Infection Management Package (EIMP) Intervention

The EIMP intervention consisted of screening and treating for urinary tract infections (UTIs), sexually transmitted infections (STIs) and reproductive tract infections (RTIs) and enhanced deworming. UTIs were treated based on sensitivity patterns. Symptomatic RTIs (eg, trichomonas, bacterial vaginosis) were diagnosed with point-of-care tests and treated accordingly with their partners. For intestinal parasites, presumptive deworming was conducted at the second trimester visit with mebendazole (500 mg). At the next antenatal care visit, approximately 1 month later, stool was screened with wet-mount microscopy and targeted treatment was provided for identified parasitic infections. The infection routine care arm involved syndromic management of maternal infections according to Ethiopian Ministry of Health recommendations.

### Biospecimen collection and processing

Maternal whole blood, serum, stool, urine, vaginal swabs and breastmilk samples were collected at trimesters 1, 2 and 3, and 1–3 months postdelivery. Umbilical cord whole blood and serum, and infant whole blood and stool were also collected at birth and 1–2 months postnatal visit(s), respectively. For samples collected during the COVID-19 pandemic, all local health and prevention protocols and guidance were followed to collect and process biospecimens. Specimens were collected at each study health centre by trained laboratory technicians assisted by study nurses and transported using triple packaging containing ice packs within 48 hours of collection to the Amhara Public Health Institute (APHI) central laboratory for processing and longer storage at −80°C. A comprehensive list and timing of biospecimens collected in this study are shown in table 2.

**Table 2 T2:** ENAT study visits and biospecimen collection

Biospecimen type (collection mechanisms)	Enrolment visit (<24 week)	ANC follow-up visit (~30–34 weeks)	Birth (within 72 hours of birth)	Postnatal follow-up visit (1–6 months)*
Urine	M	M		
Vaginal swab	M	M		
Serum	M	M	C	
Whole blood (DBS)	M	M	C	I
Whole blood (VAMS)	M	M	C	I
Stool (Genotek)	M	M		M, I
Stool (TaqMan)	M	M		M, I
Breastmilk				M

* Postnatal visits were stopped prematurely due to conflict in the study region.

ANC, antenatal care; C, cord; DBS, dried blood spot; ENAT, Enhancing Nutrition and Antenatal Infection Treatment; I, infant; M, maternal; VAMS, volumetric absorptive microsampling.

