### Infant blood

#### Umbilical cord and infant dried blood spots (DBS)

DBS samples were collected from the umbilical cord after delivery and from infants at 1–3 months. After delivery of the infant and placenta, the umbilical cord was double-clamped near the placenta and baby, cut and wiped with clean and dry gauze to remove maternal blood and contaminants. Umbilical cord blood was then drawn using an 18-gauge needle mounted on a 10 mL syringe with a luer tip. Four separate blood spots were then carefully dispensed onto a Whatman card. For infants, whole blood was collected by the heel stick technique. Samples were air-dried, transported and stored using the same procedures as maternal DBS samples.

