#### Intervention effects

In our primary analysis, we will examine differences in biomarkers or ’omics profiles across the randomised intervention study arms. We will use intention-to-treat as the primary analyses where individuals are analysed according to their originally assigned study arm, and in secondary analysis, we will also explore effects of individual interventions (ie, BEP) and adherence/dose. Outcomes will be compared between the primary factors (ENP or EIMP) to determine their marginal effects (ENP vs not-ENP, and EIMP vs not-EIMP). We will estimate differences in biomarkers, using linear mixed regression models. Potential confounding bias should be minimised due to the randomised study design; however, we will assess group differences in demographic and clinical characteristics at both cluster- and individual randomisation levels, as recommended by Consolidated Standards of Reporting Trials.^28^ Baseline covariate imbalances associated with both the outcome and exposure status (p<0.10) will be included in adjusted models as potential confounders. Multiple births will be excluded from analyses using birth outcomes due to the known increased rate of preterm birth and growth restriction among multiple deliveries. When large volumes of tests are conducted for metabolomics or genomics analyses, we will use the Benjamini-Hochberg method to correct for multiple testing, as appropriate.

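### The windows given for postnatal infant sampling conflict (1–2, 1–3 or 1–6 months), and the stated covariate rule for intervention effects does not provide for age at sampling

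*Protocol article*

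**What the plan says.** The protocol article gives the postnatal window in several places.

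- **Abstract, Methods and analysis:** specimens at enrolment, then "antenatal care follow-up (third trimester), and 1–6 months postdelivery".
- **Table 2:** one postnatal column, "Postnatal follow-up visit (1–6 months", covering maternal stool and breastmilk, and infant blood and stool.
- **Biospecimen collection and processing, text:** maternal specimens "were collected at trimesters 1, 2 and 3, and 1–3 months postdelivery". The next sentence pairs cord samples with birth and infant samples with the postnatal visit: "infant whole blood and stool were also collected at birth and 1–2 months postnatal visit(s), respectively".
- **Umbilical cord and infant dried blood spots:** "DBS samples were collected from the umbilical cord after delivery and from infants at 1–3 months".

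A footnote to Table 2 adds: "Postnatal visits were stopped prematurely due to conflict in the study region". It names no centre, arm or date.

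Under Intervention effects, biomarkers are compared by linear mixed models whose terms are not listed. The one covariate rule is: "Baseline covariate imbalances associated with both the outcome and exposure status (p<0.10) will be included in adjusted models". The section on adverse pregnancy and child development outcomes is looser and allows whatever covariates are relevant to the outcome.

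ENP is assigned by cluster, with three centres per arm in the substudy. EIMP is assigned to individuals.

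**The concern.** Infant blood has three different windows, infant stool two (1–2 and 1–6 months), and maternal postnatal samples two (1–3 and 1–6 months). Planning flexibility cannot explain this, because the article describes a collection that has ended. A reader cannot tell whether the oldest sampled infant was twice or six times the age of the youngest.

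This matters because Table 3 plans metabolomics, telomere length, microbiome and enteropathogen assays on infant samples, and any such marker may move with age. Age at sampling is set after enrolment, so a rule restricted to baseline imbalances does not provide for it. If visit timing varied by centre, part of an age difference could be read as an ENP effect. Even without imbalance, age left out of the model is avoidable noise in every postnatal contrast.

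**Working it through.** The article states no sample size, power or effect size for this point, so there is no figure to reproduce. The calculations below are illustrative.

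**From the article:** windows of 1–2, 1–3 and 1–6 months; 532 dyads; six centres, three per ENP arm; EIMP randomised individually.

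**Assumed:** ages uniform over the window; equal centres with all 532 dyads sampled (m = 532/6 = 88.7 per centre); 1:1 EIMP allocation; between-centre intraclass correlation (ICC) of age 0.05, 0.20 or 0.50; marker slope 0.2–0.4 SD per month, where SD is the spread among infants of the same age.

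**Step 1, variance added by unmodelled age.** SD of age = width/√12. Added variance = (slope × SD of age)². The standard error of an individually randomised contrast grows by √(1 + added variance).

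| Window (months) | SD of age (months) | Added variance, slope 0.2 | Added variance, slope 0.4 | Increase in SE |
|---|---|---|---|---|
| 1–2 | 1/√12 = 0.289 | (0.2 × 0.289)² = 0.003 | (0.4 × 0.289)² = 0.013 | 0.2% to 0.7% |
| 1–3 | 2/√12 = 0.577 | 0.013 | 0.053 | 0.7% to 2.6% |
| 1–6 | 5/√12 = 1.443 | 0.083 | 0.333 | 4.1% to 15.5% |

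**Step 2, chance difference in mean age between arms.** For ENP, variance = (2/3) × [ICC × SD² + (1 − ICC) × SD²/m]. Example, 1–6 months and ICC 0.05: (2/3) × [0.05 × 2.083 + 0.95 × 2.083/88.7] = 0.0843, root 0.290, and × 1.96 = 0.57 months. For EIMP, SE = SD × √(4/532); with 1–6 months that is 0.125, giving ±0.25 months.

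| Window (months) | ENP, ICC 0.05 | ENP, ICC 0.20 | ENP, ICC 0.50 | EIMP |
|---|---|---|---|---|
| 1–2 | ±0.11 | ±0.21 | ±0.33 | ±0.05 |
| 1–3 | ±0.23 | ±0.42 | ±0.66 | ±0.10 |
| 1–6 | ±0.57 | ±1.06 | ±1.64 | ±0.25 |

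These are 95% ranges in months.

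**Step 3, shift in the ENP estimate at the edge of that range.** Shift = slope × age difference. For 1–6 months it runs from 0.2 × 0.57 = 0.11 SD to 0.4 × 1.64 = 0.66 SD. For 1–3 months it runs from 0.05 to 0.26 SD, and for 1–2 months from 0.02 to 0.13 SD.

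The true window therefore decides whether this is negligible or material.

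**The case against.** The strongest reply is that the article never shows a problem with age.

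- **Confounding.** A reader might infer that sampling age is confounded with arm. No section gives age by centre or arm, and the Table 2 footnote is evidence of missing visits, not of differing ages. This objection stands: the bias is a possibility, not a finding.
- **EIMP.** A reader might extend the bias to this contrast. Individual randomisation balances age in expectation, so only precision is affected. This stands.
- **Model terms.** The mixed model's terms are not listed, and a fuller analysis plan could include age. It is therefore wrong to infer that age is excluded. What remains is that the one published rule does not provide for it.
- **Secondary analyses.** The association analyses may already adjust for relevant covariates, so the point does not apply there.
- **Other samples.** Breastmilk was collected, but Table 3 lists no assay on it. The antenatal follow-up sample has a much narrower window of about 30–34 weeks and does not carry the conflict footnote, so gestational age there is at most an optional precision term.
- **Magnitude.** Quoting only the 1–6 month figures would take the worst case of an unresolved input. This stands, and all three windows are shown for that reason.

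None of this answers the contradiction between the windows, which condensing a longer protocol does not explain.

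**Conclusion.** Two things are established from the text: three incompatible windows for a completed collection, and a covariate rule for intervention effects that does not provide for age at sampling. A third is conditional: if the window was wide and timing differed by centre, the ENP contrast on postnatal infant outcomes could be biased. For EIMP the cost is precision only. Under a 1–2 month window both effects are small, with at most 0.013 SD² of added variance. Under 1–6 months the added variance is 0.08–0.33 SD², and a chance ENP imbalance could matter. These sizes rest on uniform ages, assumed slopes and assumed ICCs, none of which the article gives.

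**What to change.** 1. Reconcile the abstract, the collection text, Table 2 and the infant dried-blood-spot section with the recorded sampling dates, and state the window actually achieved for each specimen.
2. In every postnatal intervention-effect model, include exact infant age at sampling (days postpartum for maternal stool) as a prespecified term, outside the p<0.10 screen.
3. Because visits stopped early, report age at sampling and number sampled by centre and arm.

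The cost is one model term, built from birth and sampling dates, plus one descriptive table. There is a limit: with six centres, the adjustment relies mainly on age variation within centres and cannot remove other differences between them.
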